| **6. Materials and Methods** (that could best achieve the study objectives)  **6.1 Study area/setting** (description of the area or setting where the study will be conducted)  The study will be carried out in two villages in eastern Sudan. These villages have relatively stable conditions and no modifications in the applied control measures are expected. They are far from each other and matched for malaria burden, environmental factors and control measures.  The whole area is characterized by seasonal malaria transmission. The season is confined to three months of the year, October – December. The main malaria parasite is *P. falciparum* and the main mosquito vector is *Anopheles arabiensis*10. Subpatent parasitaemias persist in some individuals throughout the dry season, with re-appearance of clinical symptoms in the malaria season associated with reinfection11.  **6.2 Study subjects** (eligibility and exclusion criteria for the study subjects)  The whole residents of the two villages will be recruited into the study. The following ones will be excluded from drug testing :   - pregnant women - children < 3 year old - history of allergy to sulpha drugs - infection with *Plasmodium* species other than *falciparum*   6.3 Combination Therapy:  The antimalarial drug combinations would be: Artesunate (AS) + Sulphadoxine Pyrimethamine (S/P) + primaquine (single dose of 0.75 mg of base/kg body weight) for one group and AS + S/P for the other. These are intended to treat malaria cases, sub-patent parasitaemia and gametocyte carriage. AS and S/P are blood schizontocidal drugs active against *P. falciparum* and gametocytocidal against developing gametocytes of *P. falciparum*. The addition of premaquine is expected to clear mature gametocytes.    6.4 Study design  A community-based intervention study will be conducted in the two villages. The study will start by a baseline evaluation of malaria morbidity and mortality during the transmission season of 2003.  A cross-sectional clinical, parasitological and molecular survey will be carried out during the dry season of 2004. Villagers will be screened for malaria parasite by microscopy. Samples detected negatives by blood films will be screened by conventional nested PCR *Pfs25* primers for detection of sub-patent parasiteamia. Blood will be collected from individuals detected positive by PCR for detection of gametocyte using the RT-PCR technique.  A treatment trial will then be carried out on malaria cases and asymptomatic carriers at the end of the dry season to test the efficacy of two combinations of antimalarial drugs.They will be followedup on days 3, 7 and 14 to confirm the clearance of *P. falciparum*  sub-patent parasitaemia and gametocyte carriage.  The impact of treating sub-patent parasitaemia and gametocyte reservoir on malaria morbidity and mortality will then be evaluated by carrying out a post-intervention survey in the two villages during the next transmission season.  **6.5 Sample sizes**  **6.5.1 Sample size for detection of parasite positive individuals during the dry season:**  The prevalence of sub-patent parasitemia during the dry season is expected to be about 15%. Therefore, the whole two villages will be screened during the dry season for detection of all positives including microscopical cases and subpatent parasitaemia to give the sample size needed for treatment trial.  **6.5.2 Sample size for evaluation of the efficacy of the two combinations**  A trial with 55 subjects on each arm would have 90% power (using a significance level of 0.05) to detect a difference between treatment groups if gametocyte prevalence detected by RT-PCR after treatment is 20% or more on day 3 in AS/SP combination and 5% or less in AS/SP + PQ, allowing for 10% loss to follow up. From earlier surveys the prevalence of sub-patent parasitaemia in the dry season was expected to be about 15% therefore 650 residents of all age groups had to be screened |

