|  |
| **6.5.3 Sample size for detection of the impact of treatment on malaria morbidity and mortality**  Based on the previous records the prevalence in the two villages is expected to be around 10%. Therefore, 216 residents from each village, out of the total of 500, will be examined to detect prevalence between 5 - 15 % at 5% level of significance with a design effect of 2.  The sample sizes were calculated using Epi-Info 2002 computer programme.  6.6. Sampling technique and randomization  Persons who were positive by PCR in the dry season will be enrolled in the study for measuring the efficacy of each combination. The list of eligible participants will be sorted according to village and age, to achieve an implicit stratification. The allocations for this ordered list will be generated using restricted randomization with a block size of 12 in Stata version 7 (Statacorp, Texas)  Simple random sampling technique will be used for the selection of the sample size needed for detecting the impact of the treatment on malaria morbidity.  6.7. Data Collection methods, instruments used, measurements  6.7.1.Describe the instruments used for data collection (questionnaire,observation recording form, etc..), studied variables included in these instruments, and methods used to test for the validity and reliability of the instrument.   - Clinical data will be collected by a medical doctor using a questionnaire. - Thin and thick blood films will be collected on slides by finger brick - A parallel drop of blood will be collected on filter paper from the same finger brick for screening by conventional nested PCR technique. - Microvet tubes will be used to collect 150 ul of blood by finger brick from PCR positive individuals only. Samples will be used for detection of subpatent gametocytes by RT-PCR.     6.7.2.Techniques used should be briefly described and referenced  Thin and thick blood films will be stained and used for species identification and parasite density estimation13.  **Detection of low level *P. falciparum* infection during the dry season**  *P. falciparum* DNA will be extracted from filter papers of microscopically negative blood samples14.  Nested PCR will then be used to detect low level *P. falciparum* infections that prevail during the dry season15. Principal genes to be detected are *Pfs*25 and *Pfg*377, which encode gametocyte specific proteins. Results will then be visualized using gel electrophoresis. Detection of gametocytes using RT-PCR RT-PCR method will be used for detection of sub-patent gametocytemia during the dry season16, 17. Briefly, blood samples collected for RNA isolation and RT-PCR of *Pfs25* and *Pfg377* will first be left at room temperature for 30 minutes, to allow exflagellation and microgamete formation. The plasma and the buffy coat will be removed and the red blood cells stored at -70°C. Total RNA will be isolated using RNA isolation kits. RT-PCR of RNA will then be carried out.   - - 1. **Study definitions (eg case definition) should be mentioned.**   Clinical malaria includes those with microscopically diagnosed *P. falciparum* and clinical symptoms.  Sub-patent parasitaemia includes those detected positive by PCR  Gametocyte reservoirs include those detected positive by the RT-PCR.  **6.8.Data Management and Statistical Analysis**  (Describe the overall plan and tests used for data analysis and statistical package used)  The efficiency of the two treatment regimens will be assessed by comparing the proportions detected positive for asymptomatic infections before and after treatment. Comparison will be done using chi-square test and the significance of the results will be measured by the *P-value*.  Malaria prevalence and percent of mortality will be determined from data collected during the transmission season survey. They will be used for evaluation of the intervention by comparing them between the two villages and with data of the previous transmission season for every village. Comparison will also be done by chi-square test.  The data will be analyzed using SPSS (Statistical Package for Social Science) version 10. |

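### Section 6.8 applies an ordinary chi-square to results that come wholly (before/after treatment) or probably partly (season on season) from the same people, ignoring within-person dependence

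*Protocol*

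**What the plan says.** Section 6.8 names one kind of test throughout.

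- **Before/after treatment.** The efficiency of the regimens is judged by "comparing the proportions detected positive for asymptomatic infections before and after treatment. Comparison will be done using chi-square test". Under section 6.6, "Persons who were positive by PCR in the dry season will be enrolled in the study", and section 6.4 has the treated people "followedup on days 3, 7 and 14 to confirm the clearance". Before and after results are therefore from the same individuals.
- **Season on season.** Malaria prevalence and mortality are compared between the two villages, and with "data of the previous transmission season for every village. Comparison will also be done by chi-square test". Section 6.5.3 states that "216 residents from each village, out of the total of 500, will be examined", and section 6.6 adds that "Simple random sampling technique will be used for the selection of the sample size" needed to detect the impact on morbidity. Section 6.5.3 also applies a design effect of 2.

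The protocol gives neither the size nor the sampling method of the 2003 baseline survey. It does not say whether the same or fresh residents are examined in the two seasons.

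**The concern.** The ordinary chi-square takes the variance of a difference between two proportions to be that of two separate samples. When the same person contributes to both proportions and the results are positively correlated, the true variance of the change is smaller. Considering that dependence alone, the test is conservative and can miss a real fall.

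The season contrast is one of only two by which 6.8 evaluates the intervention, and the protocol expects good results to lead to a recommendation to the national control programme. Because 6.8 names the test, this is not a detail left open for a later analysis plan.

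**Working it through.** **1. The plan's own figure.** Precision formula for 10% ± 5 points: 1.96² × 0.10 × 0.90 / 0.05² = 138.3. Finite population of 500: 138.3 / (1 + 138.3/500) = 108.3. Times the design effect of 2: 216.7. The stated 216 reproduces.

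**2. Before/after, PCR parasite positivity.** Enrolment requires a positive PCR. Taking that result as the before value, p₁ = 1, so p₁(1 − p₁) = 0 and the within-person covariance is 0. Pairing removes no variance. With 50 of 50 positive before:

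| Positive after | Chi-square p | McNemar p | Exact McNemar p |
|---|---|---|---|
| 45/50 | 0.022 | 0.025 | 0.063 |
| 40/50 | 0.0009 | 0.0016 | 0.0020 |

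The paired test gains nothing here. With few discordant pairs, the exact version can fall on the other side of 0.05.

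**3. Before/after, RT-PCR gametocyte carriage.** Not every PCR-positive person need carry gametocytes, so the baseline can be below 100%. The protocol gives neither a baseline carriage rate nor a within-person correlation (rho). I assume 40% falling to 20% and rho of 0.2 to 0.5. Evaluable per arm: 55 × 0.9 = 49.5, about 50. The share positive both times is 0.4 × 0.2 + rho × √(0.24 × 0.16). Simulated power at two-sided 5%:

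| rho | Chi-square | McNemar |
|---|---|---|
| 0.2 | 60% | 69% |
| 0.3 | 61% | 74% |
| 0.5 | 63% | 89% |

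With no change (30% both times), the chi-square rejects about 3% of the time at rho 0.2 and 0.6% at rho 0.5, instead of 5%.

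**4. Season on season.** Suppose both surveys are independent simple random draws of 216 from the same 500. Expected overlap is 216 × 216 / 500 = 93 people, a fraction f = 0.432. Take the protocol's 10% falling to an illustrative 5%, leaving the design effect aside.

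- Chi-square: the null standard error is √(2 × 0.075 × 0.925 / 216) = 0.0253. Without overlap, the true standard error is √((0.09 + 0.0475)/216) = 0.0252. Power = Φ((0.05 − 1.96 × 0.0253)/0.0252) ≈ 51%. It stays about 51% at every rho below.
- Allowing for overlap: variance = (0.09 + 0.0475 − 2 × 0.432 × rho × 0.0654)/216, where 0.0654 = √(0.09 × 0.0475). Power = Φ(0.05/SE − 1.96).
- Type I error of the chi-square from overlap alone: 2Φ(−1.96/√(1 − 0.432 × rho)).

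| rho | SE | Power allowing for overlap | Chi-square type I error |
|---|---|---|---|
| 0.1 | 0.0247 | 53% | 4.5% |
| 0.2 | 0.0242 | 54% | 4.0% |
| 0.5 | 0.0225 | 60% | 2.7% |

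With no overlap both tests have about 51% power, and nothing is lost.

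**5. The design effect.** If the design effect of 2 in 6.5.3 is real and the test ignores it, type I error is 2Φ(−1.96/√2) = 16.6%. Net of the 43% overlap, 2Φ(−1.96/√(2(1 − 0.432 × rho))) gives 15.7% at rho 0.1 and 11.8% at rho 0.5. This pulls in the opposite direction to step 4.

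**The case against.** The case on the other side has several parts.

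- *Before/after may not be the efficacy test.* Section 6.5.2 sizes the trial on a difference between arms on day 3, for which an ordinary chi-square suits. This stands for the between-arm contrast. Section 6.8 nevertheless words the comparison as before and after treatment.
- *Chi-square could mean McNemar's chi-square.* The wording does not exclude it for before/after. For the seasonal paragraph it is not a natural reading, because the same test also covers the two villages, whose residents cannot be paired.
- *The power loss does not apply to the outcome 6.8 names.* This stands for parasite positivity. The loss is limited to gametocyte carriage, which is the outcome behind the sample size in 6.5.2.
- *Overlap between seasons is not documented.* This stands, so the season result is conditional. Chance overlap is also a minority, 43%. A reader might infer that the contrast is mainly within-person; the protocol does not say that anyone is re-examined.
- *A correlation of 0.5 is extreme.* For 10% falling to 5% it means 37.7% of earlier positives are positive again, against 1.4% of earlier negatives. At rho 0.2 or less the seasonal gain is only about 2 to 4 points.
- *The direction of error is not established.* A reader might infer that the true type I error lies below 5%. That holds for person-level dependence alone. The protocol combines simple random sampling with a design effect of 2, so whether clustering is real is itself unclear.

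**Conclusion.** The point holds in limited form. Section 6.8, read naturally, uses a test that ignores within-person dependence in one contrast that is fully paired and in another that probably overlaps.

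- **Gametocyte carriage, before/after:** the test is conservative and loses roughly 8 to 26 percentage points of power, under an assumed 40% to 20% fall and rho of 0.2 to 0.5.
- **Parasite positivity, before/after:** no power is lost, provided the enrolment PCR is the before value.
- **Season on season:** a loss of about 2 to 9 points at rho 0.1 to 0.5 if both surveys are independent draws of 216 from 500, and none without overlap.

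The documents do not support a blanket statement that all the P-values in 6.8 are too large or that power is lost throughout. The between-village and between-arm contrasts involve different people and are not affected by this point.

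**What to change.** In section 6.8:

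1. For any within-arm before/after statement, use McNemar's test with a paired confidence interval for the change, in exact form when discordant pairs are few.
2. For season-on-season prevalence, state whether the surveys use the same or fresh residents and link them by resident ID. Use a GEE or other robust-variance model that allows for residents seen in both seasons and for the clustering implied by the design effect. Clustering on household, which contains the resident, would cover both.
3. Keep the ordinary chi-square for contrasts between different people, such as the randomised arms on day 3.
4. Do not apply pairing to mortality, since anyone seen in both surveys survived the first.

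Re-examining a fixed cohort is a design preference and is not needed to correct the analysis.

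Cost: resident and household identifiers must be kept and linked, which the protocol does not mention, and the analysis takes slightly more work. No participants or visits are added.

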| 1. Ethical Considerations    1. Informed consent form (If needed, please attach extra documents)  - Preliminary meetings will be held with the community leaders to inform them about the project and its objectives and to ask for their permission and collaborating in passing the message to the community. - A signed informed consent form will be collected from householders stating their agreement to participate. Even within each household, blood samples will be collected from those who are willing to participate. - Blood samples will be collected by a qualified laboratory technician with experience of more than 15 years in this field. This will be done under supervision of a medical doctor. - Clinical investigations for all patients, including those with common diseases, during every survey will be carried out by a medical doctor. He will also be responsible for prescription of drugs and very close clinical monitoring specially for those who will be given antimalarial drugs. - The principal investigator is committed to provide drugs for malaria and for other common diseases to those who will be detected sick during the surveys.      - 1. Institutional ethical clearance   Do you have an ethical review board in your institution: Yes [ ] No [ X ]  If no, then the ethical clearance of the Ministry of Health could be accepted.  (To be amended in case of initial acceptance by the selection committtee) |
| 1. Other funding agency   Is your study funded by another funding agency: Yes [ x ] No [ X ]  (specify the agency and available funds)  TC grant from the IAEA. |

| **12. Timeframe of research activities** (please indicate the activities to be conducted and check the corresponding month) | | | | | | | | | | | | |
| --- | --- | --- | --- | --- | --- | --- | --- | --- | --- | --- | --- | --- |
| Activity | 1st QUARTER | | | 2nd QUARTER | | | 3rd QUARTER | | | 4th QUARTER | | |
|  | M1 | M2 | M3 | M4 | M5 | M6 | M7 | M8 | M9 | M10 | M11 | M12 |
| ***Transmission season of 2003 survey*** |  |  |  |  |  |  |  |  |  | **X** | **X** |  |
| ***Dry season field survey*** |  |  | **X** |  |  |  |  |  |  |  |  |  |
| ***Nested PCRs*** |  |  |  | *X* | *X* |  |  |  |  |  |  |  |
| ***Samples for RT-PCR*** |  |  |  |  | ***X*** |  |  |  |  |  |  |  |
| ***RT-PCRs*** |  |  |  |  | X | X |  |  |  |  |  |  |
| ***Submission of the Progress Report*** |  |  |  |  |  | X |  |  |  |  |  |  |
| ***Pre-transmission field survey*** |  |  |  |  |  |  | *X* |  |  |  |  |  |
| ***Treatment &***  ***Drug testing*** |  |  |  |  |  |  | X | X | X |  |  |  |
| ***Transmission season survey*** |  |  |  |  |  |  |  |  |  |  | ***X*** |  |
| ***Submission of the Final Report*** |  |  |  |  |  |  |  |  |  |  |  | X |

| **13. Outline of budget**    Total amount of budget: US$* 10 000 | |
| --- | --- |
| **Budget breakdown:** | **Budget (US$)** |
| Personnel**  _ Medical doctor  _ Two Technicians  _ Research assistant  _ Driver  The team will be involved in four field surveys, 5 days each | **2 000** |
| Supplies and Equipment  _ Reagents  _ Disposable  _ Chemicals  _ Consumables | **2 000** |
| Local Travel  To cover expenses of travel to the study area for four surveys (5 days each) and working there between the village and the field station in Gadarief town. | **3 500** |
| Patient Costs  Mainly for drugs | **1 500** |
| Training |  |
| Others (please, specify and justify briefly)  _  _  _  _ |  |
| **Total** | **9 000** |

*Not exceeding 10,000 US$

** Only a limited proportion of the funds should be allocated to the personnel

| **14. Other information (if needed, please add any other information)** |
| --- |
| **15. Annexes (Data collection instruments, elaboration on methods and procedures to be used, etc..) (Please attach the related documents)** |
